### Data management and quality assurance

The research assistant will be trained on how to approach eligible women, and how and when to contact them for follow up and data collection. Training entails familiarizing her with all the necessary documentation, including enrollment and consent forms, and consenting in accordance with the ethical principles of the Belmont Report. Demonstration and training on the use of the syringe will also be performed.

### Sample size

Based on data from a previous breastfeeding clinical trial that we conducted, 45% of women continue to breastfeed exclusively for 1 month postpartum [21]. We hypothesize that in women with inverted nipples, 40% of the experimental group and 5% of the control group will be exclusively breastfeeding at 1 month. To have 90% power and 5% type I error, and using the online calculator available at http://powerandsamplesize.com/Calculators/Compare-2-Proportions/2-Sample-Equality, we will need 25 women in each group to detect this 35% difference in the exclusive breastfeeding rates between the two groups.

In our recent breastfeeding support trial [21], the attrition rate was 40%. Since women with inverted nipples face more difficulties in breastfeeding than women with normally everted nipples, we hypothesize that 50% attrition rate would be a reasonable assumption for the proposed study. To account for a potential attrition rate of 50%, we inflated the sample size to become 100 women in total.

### Statistical methods

We will compare continuous variables using Student’s *t* test and categorical variables using Chi square test. Non-parametric tests will be used to analyze variables with skewed distribution or when the number of analyzed subjects is less than 30. We will calculate the crude rates of exclusive breastfeeding and mixed feeding at 1, 3, and 6 months in both groups. The 95% confidence intervals for the crude rates of breastfeeding will be computed using the normal approximation to the binomial distribution. We will also conduct multivariable logistic regression analysis to investigate the association between exclusive breastfeeding at 1 month (dependent variable) and the use of the inverted syringe (predictor) adjusting for potential confounders such as the grade of inverted nipple. Missing data will be imputed using last observation carried forward for the breastfeeding outcomes at 1, 3, and 6 months if breastfeeding was discontinued on last follow-up, the average value for continuous variables, and random replacement to maintain proportions for categorical variables, as appropriate. We will conduct sensitivity analysis with and without the imputed missing data to assess the impact of missing data on the primary outcome. We will also conduct repeated measurement analyses using generalized estimating equations (GEE) to explore the effect of the intervention over time. Blinded, intention to treat analysis will be conducted using the Statistical Package for Social Sciences (SPSS) version 24. A *p* value of < 0.05 will indicate statistical significance.

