## Background

Breastfeeding confers several health benefits to infants and their mothers, including protection from infectious and chronic diseases, improved child cognition, development, and intelligence, and decreased risks of maternal depression and malignancies [1–5]. As such, breastfeeding is recommended as the exclusive nutrition for the first 6 months of the infant’s life, with continuation until 2 years complemented with solid foods [6–8]. However, women with inverted nipples often have difficulties in maintaining breastfeeding due to improper infant latching that my cause insufficient milk extraction and poor infant satiety, thus leading to early termination of breastfeeding. Congenital inversion of the nipple, the most common nipple deformity, is due to early developmental arrest [9], with an estimated prevalence of about 10% [10]. However, nipple inversion can also be acquired secondary to mastitis, macromastia, carcinoma, or breast reduction, or can be associated with congenital syndromes such as Robinow and MR/MCA syndromes [11]. Han and Hong categorized the severity of inverted nipple into three grades. In grade 1, the nipple is easily pulled out manually, maintains good projection, and has minimal fibrosis. Grade 2 includes the majority of inverted nipple cases in which the affected nipple can be pulled out manually but fails to maintain projection and has moderate fibrosis beneath it. Grade 3 constitutes the rarest type of inverted nipples, which cannot be pulled out manually due to severe fibrosis [12].

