#### Secondary outcome measures

Secondary outcomes include differences between the two groups in the rates of nipple eversion at 1 month, successful latching of the infant on mother’s breast at 1 month, exclusive breastfeeding at 3 and 6 months, mixed feeding at 1, 3, and 6 months, breastfeeding-associated complications such as sore nipple, mastitis, pain, bleeding, and breast engorgement at 1 week, 1, 3, and 6 months postpartum. Other secondary outcomes are maternal satisfaction with breastfeeding assessed at 1 week postpartum using the validated Maternal Breastfeeding Evaluation Scale [18, 19], and maternal quality of life assessed at 1 month using the validated Postpartum Quality of Life instrument [20] (Fig. 1).

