### Data collection

At baseline, we will collect information on socio-demographics such as maternal age, parity, education, employment, family monthly income, previous breastfeeding, and longest duration of previous breastfeeding if present. Data on gestational age, mode of delivery, newborn’s gender, birth weight, APGAR score, and nursery admission status (regular vs intensive care), as well as grading of maternal nipple inversion will be recorded.

On the first day postpartum, the following information will be collected: exclusive breastfeeding (yes/no), use of artificial milk (number of feeds in 24 h, justification), sore nipple (yes/no), pain while breastfeeding (yes/no), compliance with the use of the syringe technique before each breastfeed (experimental group only), and the use of other conservative methods to pull out the nipple (in both groups).

On the third and seventh days postpartum, we will call the participants to remind them about documentation in the diary, collect data about maternal breastfeeding evaluation (day 7 only), and address any questions.

The diary will be collected at 30 and 40 days during the participant’s postpartum visit to her obstetrician. We will also administer the Postpartum Quality of Life instrument, and collect data on the infant’s weight at month 1 from the infant’s health record. The eversion of the nipple will also be assessed by the research assistant during this visit.

On months 3 and 6 postpartum, we will call the participants to collect information on infant feeding methods, adverse events, and infants’ weight at 3 and 6 months.

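### Nipple eversion at 1 month is compared without regard to baseline grade, probably at some cost in precision

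*Protocol article*

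**What the plan says.** The secondary outcomes in the protocol article include "differences between the two groups in the rates of nipple eversion at 1 month". Eversion has one assessment after baseline, at the postpartum visit to the obstetrician (Data collection): "The eversion of the nipple will also be assessed by the research assistant during this visit".

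Statistical methods compares "categorical variables using Chi square test". The only model said to adjust for grade is a logistic regression with exclusive breastfeeding at 1 month as dependent variable. The generalized estimating equations are meant to explore the effect over time, which does not fit an outcome assessed once after baseline. The abstract mentions regression in general but no model for eversion.

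Grade is available: at baseline, "grading of maternal nipple inversion will be recorded". The Background describes the two enrolled grades. For the first: "In grade 1, the nipple is easily pulled out manually, maintains good projection, and has minimal fibrosis". A grade 2 nipple "can be pulled out manually but fails to maintain projection". The Randomization section describes 1:1 allocation from a computer-generated sequence and states no stratification by grade.

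**The concern.** Grades 1 and 2 are separated largely by whether a nipple stays out once it has been drawn out. That makes grade a graded baseline measure of the property assessed at 1 month, and a plausible strong predictor of it. The plan treats grade as a potential confounder for exclusive breastfeeding, a more distant outcome that also counts expressed milk, but not for eversion, where the link should be closer.

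Two things are at stake. Ignoring a strong predictor of a binary outcome costs power. And in a small trial without stated stratification, one arm may by chance receive more grade 1 women; the crude comparison then reports part of that difference as a treatment effect.

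**Working it through.** **The plan's own figure.** The only sample size stated is for exclusive breastfeeding at 1 month. With 40% v 5%, two-sided 5% (sidedness assumed) and 90% power, the unpooled formula gives n = [0.40×0.60 + 0.05×0.95] × (1.960 + 1.282)² / 0.35² = 24.66, so 25 per arm. With 50% attrition, 25/0.5 = 50 per arm, 100 in total. Both stated figures reproduce. No power is claimed for eversion. The range to examine is therefore 25 per arm (if attrition is as planned) to 50 per arm (all randomised women).

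**Inputs not in the documents (assumed).** Control eversion rate by grade, a common odds ratio (OR) of 3 or 4, and a grade 1 share of 50% or 30%. The Background says most cases are grade 2, so 30% may be nearer.

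**Tests compared.** Crude Pearson chi-square against the Mantel-Haenszel test stratified by grade, neither with continuity correction. In grade g, let m and k be the numbers in the intervention and control arms, N = m + k, x the everted in the intervention arm and M all everted. The stratified statistic is [Σ(x − mM/N)]² / Σ{mkM(N − M)/[N²(N − 1)]}, referred to chi-square on 1 df. Each cell used 200,000 simulated trials with unstratified allocation (simulation standard error about 0.1 point).

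**Power, crude v stratified (%)**

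| Control eversion, grade 1 / grade 2 | Grade 1 share | 50 per arm, OR 3 | 50 per arm, OR 4 | 25 per arm, OR 3 | 25 per arm, OR 4 |
|---|---|---|---|---|---|
| 80 / 20 | 50% | 44.5 v 58.0 | 63.1 v 77.6 | 27.3 v 32.2 | 39.1 v 47.4 |
| 80 / 20 | 30% | 53.1 v 63.2 | 74.3 v 83.3 | 32.8 v 35.8 | 48.4 v 53.2 |
| 70 / 30 | 50% | 62.3 v 67.9 | 80.5 v 85.5 | 38.3 v 39.2 | 53.4 v 55.7 |
| 70 / 30 | 30% | 68.6 v 71.5 | 86.1 v 88.5 | 43.6 v 42.4 | 60.3 v 60.0 |
| 90 / 40 | 50% | 47.2 v 55.7 | 65.1 v 73.7 | 27.2 v 30.9 | 38.9 v 43.8 |
| 90 / 40 | 30% | 58.5 v 65.7 | 77.5 v 83.4 | 35.4 v 37.8 | 49.9 v 53.6 |
| 50 / 30 (weak) | 50% | 75.6 v 75.0 | 90.8 v 90.9 | 49.3 v 45.0 | 66.7 v 63.3 |
| 40 / 30 (weak) | 50% | 78.0 v 76.5 | 92.8 v 92.1 | 51.8 v 46.3 | 70.3 v 65.1 |

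In the six strong-link rows the change is about +3 to +15 points at 50 per arm and about -1 to +8 at 25. In the weak-link rows it is between 0 and about -1.5 at 50 per arm and about -4 to -5 at 25 (-3.4 to -5.5 unrounded).

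**Type I error (OR 1).** Over all trials, the crude test rejects in about 5% to 6.5% and the stratified test in about 5%. Part of the crude test's apparent advantage at 25 per arm under a weak link is this slight liberality.

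**Chance imbalance.** A difference of d in the grade 1 share shifts the crude eversion difference by d × (rate in grade 1 − rate in grade 2). With d = 20 points and 80/20 this is 0.20 × 0.60 = 12 points; with 40/30 it is 0.20 × 0.10 = 2 points. At 25 per arm and an equal grade mix, an imbalance of 20 points or more arises in about 20% of trials. In those trials, with 80/20 and no treatment effect, the crude test rejects in about 17% and the stratified test in about 5%. At 50 per arm such an imbalance arises in about 6% of trials.

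**The case against.** The strongest reply is that nothing here is wrong. A chi-square test on randomised groups is valid, eversion is a secondary outcome with no stated power, and the regression on the primary outcome already includes grade. Covariates for secondary outcomes might also be left to a fuller document. The first three points stand and limit the weight of this one. The last does not: the article names a test for categorical outcomes and names the one outcome that gets grade adjustment, so the point concerns a stated method.

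Four stronger readings are tempting but unsupported.

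- A reader might infer that grade is by definition the baseline value of the outcome. Every enrolled nipple is inverted, so on a yes/no eversion scale all women start alike. Grade describes response to manual traction and degree of fibrosis. It is a related, graded measure, and the documents give no eversion rate by grade.
- A reader might infer from the 17% figure that the crude test is invalid. That figure is conditional on the more imbalanced fifth of trials at 25 per arm, under an assumed strong link.
- A reader might infer that stratifying cannot hurt. The weak-link rows show that it can.
- A reader might extend the argument to latching. No section links latching with grade, and no calculation was made for it.

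**Conclusion.** The point holds as a matter of efficiency and of conditional bias under imbalance, not of validity. The plan leaves out, for eversion, the baseline variable that its own Background ties most closely to that outcome, and neither the stated design nor the stated analysis makes up for it.

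The size is uncertain. The benefit is clear at 50 per arm if grade is strongly prognostic. At the 25 per arm that the planned attrition implies, it is modest at best and can be slightly negative. All power figures rest on assumed eversion rates, odds ratios and grade mix. The grade definitions make a strong link plausible but do not establish it. The primary comparison is not affected.

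**What to change.** Pre-specify, for nipple eversion at 1 month, the Mantel-Haenszel test and Mantel-Haenszel risk difference with 95% confidence interval, stratified by baseline grade (1 v 2) and comparing the randomised groups. Add a rule that gives each woman one grade when her two nipples differ, for example the worse grade. Keep the crude chi-square as supportive. The same analysis of latching is optional.

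The cost is a sentence or two in the analysis plan, with no new data, since grade is already recorded. The downside is a small loss of power if grade turns out to be weakly prognostic. Fixing the choice before results are seen also avoids adding adjustment only if an imbalance appears.

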### Randomization

We will randomly allocate eligible women to one of two parallel groups (experimental and control) in a 1:1 ratio according to a computer-generated random sequence. An independent statistician will prepare a set of sequentially numbered opaque sealed envelopes of the allocation group according to the generated random sequence to preserve randomization concealment. A participant’s group allocation will be revealed after verifying that the inclusion/exclusion criteria are met, and after written consent is obtained on the first day postpartum. This will avoid any selection bias introduced by the investigator knowing the allocation of the next subject.

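### Normal-approximation 95% intervals are fixed for a control rate planned at 5%, where they cover about 72% (25 women) to 92% (50 women), and the logistic model has no fallback when no control woman has the event

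*Protocol article*

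**What the plan says.** The protocol article, Statistical methods, names the interval method for the feeding rates at 1, 3 and 6 months in each group: "The 95% confidence intervals for the crude rates of breastfeeding will be computed using the normal approximation to the binomial distribution". The same section adds a regression: "We will also conduct multivariable logistic regression analysis to investigate the association between exclusive breastfeeding at 1 month (dependent variable"), with syringe use as predictor and nipple grade given as an example of an adjustment variable. The software is SPSS 24.

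The Sample size section sets the conditions under which these methods must work. It expects that "40% of the experimental group and 5% of the control group will be exclusively breastfeeding at 1 month", states that "we will need 25 women in each group to detect this 35% difference in the exclusive breastfeeding rates between the two groups", and then allows for loss: "To account for a potential attrition rate of 50%, we inflated the sample size to become 100 women in total". With 1:1 allocation that is 50 randomised and, at the full planned attrition, 25 evaluable women per group.

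Statistical methods gives no other interval or model for very low counts. It does switch to non-parametric methods below 30 subjects, but that rule concerns tests and leaves the interval method unchanged. Missing data are imputed under intention to treat, and a sensitivity analysis compares results with and without the imputed values.

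**The concern.** Five per cent of 25 women is 1.25 expected events, and 5% of 50 is 2.5. The normal approximation is unreliable at such counts. It can give negative limits for a rate. With no events it gives an interval of zero width, which presents a sample of 25 or 50 as if it had established a rate of exactly 0%. A published control rate would then carry a 95% label that it does not earn.

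The same sparse cell affects the regression. If no control woman has the event, an ordinary fit has no finite odds ratio for treatment, and the software prints a very large number with an unusable standard error. The stake is the reported precision of the control rate and the reported size of the adjusted effect.

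**Working it through.** **Inputs.** From Sample size: control rate 5%, experimental rate 40%, 25 evaluable of 50 randomised per group, 90% power, 5% type I error. From Statistical methods: normal-approximation interval, logistic regression. Assumed: a two-sided test, which the text does not state.

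**The plan's own figure.** The two-proportion formula with unpooled variance gives n = (1.960 + 1.282)² × (0.40×0.60 + 0.05×0.95) / 0.35² = 24.66, so 25 per group. Then 25 / (1 − 0.5) = 50 per group, 100 in total. The stated sample size reproduces and is not in question.

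**Interval.** For x events in n women the interval is x/n ± 1.96 × √[(x/n)(1 − x/n)/n]. Coverage at true rate p is the sum of the binomial probabilities of every x whose interval contains p.

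- n = 25, p = 0.05: x = 0 gives 0% to 0% and misses. x = 1 gives −3.7% to 11.7%, x = 3 gives −0.7% to 24.7%, and both contain 5%. From x = 6 the lower limit exceeds 5%. Coverage = P(1 ≤ X ≤ 5) = 1 − 0.2774 − 0.0012 = 0.721.
- n = 50, p = 0.05: x = 0 misses, and so does x = 8 or more. Coverage = P(1 ≤ X ≤ 7) = 1 − 0.0769 − 0.0032 = 0.920.
- At both sizes the lower limit is zero or negative for x = 0 to 3. P(X ≤ 3) is 0.966 at n = 25 and 0.760 at n = 50.

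| True rate | n | Normal approximation | Wilson | Clopper-Pearson |
|---|---|---|---|---|
| 5% | 25 | 72.1% | 96.6% | 99.3% |
| 5% | 50 | 92.0% | 96.2% | 98.8% |
| 40% | 25 | 93.6% | 93.6% | 97.7% |
| 40% | 50 | 94.1% | 94.1% | 97.1% |

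For single results, 1/25 gives −3.7% to 11.7% by the planned method and 0.7% to 19.5% by Wilson; 0/25 gives 0% to 0% against 0% to 13.3%.

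**Zero control events.** (1 − p)ⁿ gives 0.95²⁵ = 27.7% and 0.95⁵⁰ = 7.7%. These are the samples in which the interval collapses and an ordinary logistic fit has no finite treatment odds ratio.

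**Regression with grade added.** This was simulated with 1,500 runs per setting, group and grade in the model, no grade effect, and an assumed grade split. A finite maximum-likelihood fit did not exist in 26% to 28% of runs at n = 25 and 7% to 8% at n = 50 for splits of 50:50 or 70:30. At a 90:10 split the figures were 51% and 16%.

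**If the control rate is higher than planned.** The rates of 10% and 15% are assumptions. Normal-approximation coverage is 92% (n = 25) and 88% (n = 50) at 10%, and 90% and 94% at 15%. The chance of no event is 7% and 0.5% at 10%, and 1.7% and 0.03% at 15%.

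**The case against.** Several objections have force, and they set the limits of the point.

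- **72% and 28% are the worst planned case.** They apply if the full 50% attrition occurs and only observed outcomes are used. If all 50 per group are analysed, the figures are 92% and 8%. This stands, and the range must be shown. Even the 92% treats 50 outcomes as observed; imputed values add no real information.
- **A reader might infer that the primary result's interval is invalid.** The text does not support that. The primary outcome is the difference between groups, and the named method applies to each group's crude rate. The article fixes no interval for the difference.
- **A reader might infer that the primary analysis breaks down.** It does not. The regression is introduced as something done in addition, after the chi-square test has been named for categorical variables. With 0/25 against 10/25, chi-square gives p = 0.0004 and Fisher's test p = 0.0006.
- **A reader might infer that the model fails just when the syringe works.** The non-finite odds ratio comes from having no control event, which depends on the control rate and the number of control women. The experimental rate hardly matters: 0.60²⁵ is about 3 in a million.
- **The 5% is a hypothesis.** The previous trial cited in Sample size had 45%, and controls may use the syringe or other devices. At 10% or 15% the zero-event risk falls sharply. Interval coverage still ranges from 88% to 94%, so only the regression part of the point largely fades.
- **Ordinary maximum likelihood is not named.** It is the natural reading of multivariable logistic regression in SPSS, but it is a reading.
- **The open list of adjustment variables** is a detail that an analysis plan commonly settles, and is no finding here.

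**Conclusion.** The point holds in a limited form. The article names an interval method that does not suit the control rate on which the trial is sized. At 5%, a nominal 95% interval covers about 72% with 25 women and 92% with 50. Its lower limit is usually zero or negative, and with probability 28% or 8% it collapses to 0% to 0%. In those same samples the additional adjusted model, fitted in the ordinary way, has no finite treatment odds ratio.

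The defect lies in low-rate cells; the 40% arm is covered at about 94%. The sample size and the chi-square comparison are not affected. The figures rest on the protocol's own 5% and on 25 to 50 analysed women per group; the regression figures also rest on an ordinary fit. It should be corrected, but it does not threaten the main comparison.

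**What to change.** In Statistical methods, replace the normal approximation with Wilson intervals (or Clopper-Pearson, which is more conservative) for all crude feeding rates. Add a Newcombe or Miettinen-Nurminen 95% interval for the difference in 1-month exclusive breastfeeding, since that is the primary outcome and the scale on which the trial is sized. State that the additional adjusted model will be fitted by Firth-penalised or exact logistic regression, at least when events are sparse, with the trigger written down before the data are seen.

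The cost is a few sentences. No participant, visit or sample-size change is needed. The one practical drawback is that Firth or exact regression may need an add-on or software other than SPSS 24.

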### Outcome measures

#### Main outcome measure

The trial’s primary outcome is the difference between the two groups in the rates of exclusive breastfeeding at 1 month postpartum, whether breast milk is provided to the infant through direct latching on the mother’s breast or as expressed milk offered by cup or bottle.

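### The carry-forward rule is keyed to stopping breastfeeding rather than losing exclusivity, so, read literally, a woman last recorded as mixed feeding can be filled in as exclusively breastfeeding

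*Protocol article*

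**What the plan says.** Main outcome measure defines the primary outcome as "the difference between the two groups in the rates of exclusive breastfeeding at 1 month postpartum". Secondary outcome measures add exclusive breastfeeding at 3 and 6 months and list mixed feeding at all three times as a separate outcome. Statistical methods keeps the two states apart as well: "We will calculate the crude rates of exclusive breastfeeding and mixed feeding at 1, 3, and 6 months in both groups".

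For missing values, Statistical methods sets three rules. Breastfeeding outcomes get "last observation carried forward for the breastfeeding outcomes at 1, 3, and 6 months if breastfeeding was discontinued on last follow-up". Continuous variables get the mean. The third rule is "random replacement to maintain proportions for categorical variables, as appropriate". A sensitivity analysis with and without the imputed values is planned for the primary outcome.

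Data collection lists, for the first postpartum day, "exclusive breastfeeding (yes/no), use of artificial milk (number of feeds in 24 h, justification". The day 3 and day 7 calls are to remind women about the diary, "collect data about maternal breastfeeding evaluation (day 7 only), and address any questions". The diary, which records artificial milk feeds in both groups, is handed in at the postpartum visit. Feeding method is asked by telephone at months 3 and 6. Sample size allows for 50% attrition.

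**The concern.** The endpoint and the trigger describe different events. A woman who has added artificial milk but still breastfeeds is no longer exclusive, yet she has not discontinued. The carry-forward rule therefore does not reach her, although her last known status already bears on the outcome. The only other stated rule that fits a yes/no variable is random replacement, under which she may be entered as exclusively breastfeeding. For example, a woman mixed feeding at 1 month who misses the 3-month call could come back as exclusive at 3 months.

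Choosing a better imputation method would not by itself cure this, because multiple imputation with the same trigger would still leave these women's last status unused. With half the sample expected to be lost, a rule for lost women carries real weight.

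**Working it through.** **The plan's own figure.** Inputs from Sample size: 40% v 5%, 90% power, 5% type I error (taken as two-sided), 50% attrition. The unpooled two-proportion formula gives n = (0.40×0.60 + 0.05×0.95) × ((1.960 + 1.282)/0.35)² = 24.66, so 25 per group. Then 25/(1 − 0.50) = 50 per group, 100 in total. The stated size reproduces and is not in dispute. It means that up to 25 of 50 women per arm may need a filled or carried-forward value.

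**Which rule applies to whom, read literally.**

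| Last recorded status | Carry-forward condition met? | Stated rule |
|---|---|---|
| Stopped breastfeeding | Yes | Carried forward: not exclusive |
| Mixed feeding | No | Random replacement |
| Exclusive | No | Random replacement |
| None recorded | No | Random replacement |

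The second row is the defect: the woman's last status was not exclusive and the rule does not use it.

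**What is known before each time point.** For months 3 and 6, the 1-month status is on record, so a mixed feeder can be identified. For month 1, the article lists feeding status only on day 1. Diary data exist only if the diary is returned.

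**Illustration of size.** From the plan: 50 per arm, 25 lost per arm, observed rates 40% v 5%. These are 1-month planning rates; the article gives none for 3 or 6 months. Assumed: k lost women per arm last recorded as mixed feeding, equal in both arms, with all other lost women having stopped.

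- Observed successes: 25 × 0.40 = 10 and 25 × 0.05 = 1.25.
- Mixed feeders scored not exclusive: 10/50 = 20% v 1.25/50 = 2.5%, a difference of 17.5 points.
- Within-arm filling adds k × (0.40 − 0.05)/50 to the difference.
- The pooled fill rate is (10 + 1.25)/50 = 22.5%. Pooled filling adds k × 0.225/50 to each arm's rate and nothing to the difference.

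| k per arm | Filled as exclusive, within arm | Added to difference | Difference, within arm | Difference, pooled | Control rate, pooled |
|---|---|---|---|---|---|
| 5 | 2.0 v 0.25 | 3.5 points | 21.0 | 17.5 | 4.75% |
| 10 | 4.0 v 0.5 | 7.0 points | 24.5 | 17.5 | 7.0% |
| 15 | 6.0 v 0.75 | 10.5 points | 28.0 | 17.5 | 9.25% |
| 20 | 8.0 v 1.0 | 14.0 points | 31.5 | 17.5 | 11.5% |
| 25 | 10.0 v 1.25 | 17.5 points | 35.0 | 17.5 | 13.75% |

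At k = 25, within-arm filling returns the complete-case difference of 35 points. It never goes beyond it.

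**The planned sensitivity analysis.** Without imputed values, the lost women are dropped, and the illustration gives 40% − 5% = 35 points. Neither version uses a mixed feeder's recorded status, and the check is stated only for the primary outcome.

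**The case against.** The strongest reply is that the three rules stand side by side and are qualified by discretion. The article never says that a feeding outcome failing the carry-forward condition passes to random replacement; it could be left missing. The condition could also be shorthand for discontinuing exclusive breastfeeding. Both readings are possible, and the second may be what was meant. Neither is written, so the literal reading remains open to whoever runs the analysis.

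A reader might infer a bias of about 10 points towards the syringe on the primary outcome. The documents do not support that, for four reasons:

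- It needs 15 of 25 lost women per arm to be recorded as mixed feeding, when day 1 is the only status listed before the 1-month visit. No share of mixed feeders among lost women is given anywhere.
- It needs within-arm filling, which is not specified.
- Exclusivity at 1 month may be meant as status at that time. A mixed feeder on day 1 is then not a certain failure at day 30.
- The with/without comparison would show the effect of imputation on the primary outcome, although it would not correct the rule.

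A reader might also infer that the day 3 and day 7 calls collect no feeding status. A condensed article may leave form content to the full protocol, so that cannot be counted as a fault.

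These points limit the size and reach of the problem. The mismatch between trigger and endpoint stands.

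**Conclusion.** The rule as written does not match the endpoint. Followed literally, it lets women whose last recorded status was mixed feeding be scored as exclusively breastfeeding. This matters most for exclusive breastfeeding at 3 and 6 months, where the earlier status is on record and no with/without-imputation check is stated. For the 1-month outcome it reaches only women with artificial milk on the day-1 record or in a returned diary.

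The size is illustrative: 3.5 points on the difference for each 5 such women lost per arm under within-arm filling. Under pooled filling there is no change in the absolute difference, but both arms' rates are raised. These figures rest on the plan's 40% and 5%, 50 women per arm, and an assumed number of such women that is equal between arms. The direction and size of any bias cannot be settled from the article.

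**What to change.** Reword the missing-data sentence in Statistical methods along these lines:

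- For exclusive breastfeeding at 1, 3 and 6 months, carry forward a status of not exclusive for any woman whose last recorded feeding was mixed or artificial.
- For any or mixed feeding, carry forward a status of stopped for women who had discontinued.
- Use other imputation only for women still exclusive, or with no recorded status, at last contact.

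Optionally, record current feeding status (exclusive, mixed, stopped) in the day 3 and day 7 calls if the forms do not already do so. The 1-month rule would then have more than the day-1 record to act on.

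The cost is a short rewording and, if wanted, one question in two calls already planned. The downside is that women who return to exclusive feeding after last contact are counted as not exclusive. This matters most when only a day-1 record is carried to 1 month.
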